## Methods

2

### Setting

2.1

The intervention is designed to be delivered at Danish primary schools (public, private, or free schools) by teachers to their regular class groups. With the Danish inclusion policy, most class groups will have children with special needs. However, in the pursuit of creating comparable treatment groups, whole class groups for children in special education or with significant learning disabilities will not be included. After the assignment to intervention and control groups, the teachers involved will attend separate online information meetings. They will then get access to the teaching materials on a digital platform including podcasts and activities as explicated below. Data will be collected at the schools in an environment known to the children to improve validity and to minimize the inconvenience for participants.

### Study population and eligibility criteria

2.2

Teachers of class groups from 4th and 5th grade will be invited to take part (children aged 9–12 years). As teachers in Denmark often work in teams, whole year groups are encouraged to take part, and the material includes topics designed to be discussed between teachers during subject-specific team meetings (The Danish Evaluation Institute, 2021). Teachers agree to partake on behalf of their entire class group, and all children in an intervention class group take part in the intervention. Children with mild learning disorders or limited Danish proficiencies with parental consent to participate in assessments will be supported by researchers when completing questionnaires.

### Intervention and comparator

2.3

The 10-week teacher-led intervention is structured into five modules, which are made up by the three central subcomponents of EF (response inhibition, working memory and cognitive flexibility) (Friedman and Miyake, 2017) and the related skills of self-regulation and metacognition (Buttelmann and Karbach, 2017; Hofmann et al., 2012). Whereas the first four modules are based on foundational EF skills, metacognition may be perceived as an advanced skill developing later in childhood (Dawson, 2021), which is why this skill is the last to be explored during the intervention. Each of these five pillars are to be explored and implemented into regular classes during two school weeks (Table 1). Participating teachers get access to the material on a digital platform made available by publishing company Forstå (Forstå-Gratis undervisningsforløb og undervisningsmaterialer, n.d.).

**Table 1 tab1:** Content and narrative of the five intervention modules.

	Module 1: Impulse control		Module 2: Working Memory		Module 3: Cognitive flexibility		Module 4: Self-regulation		Module 5: Metacognition	
	Week 1	Week 2	Week 3	Week 4	Week 5	Week 6	Week 7	Week 8	Week 9	Week 10
Narrative	Presentation of Sofus and the circumstances		Examine the crime scene		Explore suspects (different angles and motives)		The situation is coming to a head–stay calm!		The mystery culminates	

The teaching materials are developed by authors [name] and SV and consist of knowledge and research-based suggestions for teachers and an educational narrative with associated activities for the pupils.

From a pupil perspective the material revolves around the detective Sofus. When they first meet Sofus, someone has rummaged through his office, and he needs the help of the class group to solve the mystery ahead of him. In the narrative, someone shuts down the internet, which adds elements of technology education and reflections on digital distraction, privacy, and climate. The story works as a common third for pupils and teachers to work with, with the obvious purpose of helping Sofus and the indirect purpose of transferring and internalizing the strategies that he needs and uses to themselves.

In Table 2, the activities connected to each EF skill are described briefly. The modules are available to teachers in a sequential order progressing from more basic EF skills and finishing with metacognition which develops later in childhood and can be conceived as a more advanced EF (Dawson, 2021).

**Table 2 tab2:** Progressive intervention activities by executive function and SOFUS skills.

EF skill	SOFUS skill	Week	Activities
Impulse control	Strategies Make a plan Stop Stay calm	1	Sofus’ Office: Gather clues and leads (identify potentially relevant items). Simon Says (variation): React only to instructions given in a certain voice or manner; ignore others.
		2	Double Circles: Discuss who needs the internet, what do you like to do when online, and what would happen if the internet was shut down? Forbidden Words: Explain certain words to a partner for them to guess without mentioning three descriptor words printed in red. In round two, use only mime.
Working memory	Overview Use memos Follow your plan Organize	3	Who’s Mar? Come up with as many names as possible starting with “Mar.” The Library: Sort leads and clues into categories to create an overview.
		4	Using Memos: Look at the pictures or a selection of things and recall them after they are covered. Code Language: Try to decode secret messages using a symbol key and learn some of the symbols by heart.
Cognitive flexibility	Flexibility In other eyes Adjusting Get ideas	5	Plan the Route: Plan Sofus’ route to visit suspects taking the order of important events into account. Looking into Suspects: Identify who the suspects are based on Sofus’ notes?
		6	In the Eyes of the Suspects: Divide the class into interviewers and interviewees; interviewees role-play as one of the two suspects. Alibies: Work out what the evidence says about the alibies of the suspects by flipping the text in your head.
Self-regulation	Perseverance Patience Practice makes perfect Determination	7	Calming Down Sofus: Discuss strategies for managing anger using Sofus’ frustration as a case. What helps you to calm down when angry? Thought Channels: Pretend that you can shift your thoughts with a controller. Talk about three elements in the picture one at a time and shift when asked to.
		8	Help Sofus Recap and Review: Reflect on what has happened so far; have any leads or clues been left out and need following up. Sofus’ Boss: Use her plane ticket to work out whether she has an alibi.
Meta-cognition	Self-reflection Who am I? What is going well? What is hard?	9	Self-Reflection: What things are currently going well and which things you would like to become better at. The Negotiation: What agreement can Sofus make with his colleagues about the internet? How can they use it in a responsible, controlled way?
		10	What would the others think: When seeing things from other characters’ points of view, what might they think about the deal made last week? Cleaner’s room: Examine the notes and review all the strategies you have developed throughout the intervention period.

Sofus is a relatively common Danish name, but in this context Sofus also serves as an acronym linking directly to the intervention’s main cognitive concepts as presented in Table 3 below:

**Table 3 tab3:** The Sofus acronym and related cognitive concepts in Danish and English linked to executive functions (EF).

	**S**	**O**	**F**	**U**	**S**
Danish word	Strategier	Overblik	Fleksibilitet	Udholdenhed	Selvrefleksion
English word	Strategies	Overview	Flexibility	Perseverance	Self-reflection
EF	Inhibition	Working memory	Cognitive flexibility	Self-regulation	Metacognition

These five skills are central to the activities and the narrative. During each of the five modules, the pupils complete a selection of activities that engage the module skill in focus, resulting in leads that aid them in solving the mystery ahead. Each week there are multiple activities available, and teachers are encouraged to implement at least one activity each week. Customized illustrations were created to support and accompany each module.

The digital platform will contain all instruction material and teaching content. The topic of each of the five pillars will be introduced through 6–10-min explanatory podcasts, featuring research experts and practitioners from within the field.

In the project a teaching-as-usual control group will be included. This group will be offered to access the On Track teaching materials as soon as assessments are completed, before the materials are made publicly available.

Both groups will be offered a post-intervention presentation on the development and common challenges to EF and SR skills, and an explanation of the average class-level progress during the intervention period based on the aggregated data collected for their class.

### Intervention compliance

2.4

To monitor adherence to the program, teachers in the intervention group will receive a brief electronic survey every 2 weeks. In this survey they answer a small number of questions about which exercises they used in class and how well they worked. In addition, we can access user time use data through the publisher and send teachers a text reminder to encourage engagement if they have not accessed the platform within the last week.

### General description of assessments

2.5

Researchers and research assistants will conduct assessments in the participating schools at three time points; t_0_: 1–2 weeks prior to the intervention period, t_1_: 1–2 weeks after the intervention period, and t_2_: 4 months after the intervention period (follow-up assessment). During assessments, pupils will complete psychometric tasks and questionnaires on iPads in a room where there is space between them and minimal visual and auditory distractions. Parents and teachers will receive secure links to their questionnaires, which they can complete privately at home.

Assessments will be conducted on-site at the schools involved in the project, and intervention and control groups will be tested in parallel. Whenever possible, research assistants who are blinded to the group allocation will conduct the data collection to minimize the potential risk of bias (Higgins and Cochrane Collaboration, 2020). For practical reasons, it will not be possible to blind main researchers and participating teachers to group allocation. However, because regular teachers will implement the materials into their own classes over 10 weeks, the risk of Hawthorne effects is expected to be smaller compared to researcher-led interventions (Murnane and Willett, 2011). To enhance study validity and reliability, more than one mode of assessment is used (multi-modal), multiple informants report on each child (multi-informant) and these informants represent different contexts from the child’s everyday life (multi-setting) (Sparrow, 2010).

To ensure ethical research practices during assessments, researchers and research assistants will talk to children in a developmentally appropriate language, thereby obtaining informed consent in a manner aligned with their understanding and developmental level (Field Marilyn et al., 2004).

### Psychometric tasks

2.6

All tests will be administered by researchers and research assistants and completed on iPads (10th generation, 10.9-inch) at each school.

*d2-R* is a digital concentration and attention test (Hogrefe, n.d.) comprising 14 20-s trials, each containing 60 items (letters d or p with 0, 1, or 2 dashes above or below the letter). The participant must press as many targets as possible (d’s with two dashes) and ignore all distractors (all other letter/dash combinations). The d2-R score represents processing speed and constitutes the primary outcome measure. Due to the close relationship between the focused attention skills needed for this task and executive functions such as working memory and inhibition, the d2-R is used as a proxy measure for EF in the context of this study.

*Stop Signal Task (SST)* is a task to assess response inhibition. The participant has to inhibit their response to press the screen when occasionally presented with a stop signal amongst primarily go signals (Logan, 2015; Logan et al., 1984). We will include individual stop signal reaction times as a secondary outcome measure in our exploratory analyses.

### Questionnaires

2.7

*Demographic information:* Information on child age and sex will be collected at baseline through parent consent forms.

*Behavior Rating Inventory of Executive Function, Second Edition (BRIEF-2) Screening form* will be included in parent-and teacher reports which cover the age range of 5–18 years. This abbreviated version of the BRIEF-2 questionnaire (PARinc, n.d.) assesses EF through 12 items that are answered in a three-point Likert format with the response options “Never,” “Sometimes” and “Often” (Gioia et al., 2015). Based on Danish norm data from a group of children with typical development, there is good internal reliability with the parent and teacher report reaching a Cronbach’s *α* coefficient of 0.84 and 0.93, respectively (Ziska, 2024). The BRIEF-2 Screening form must be interpreted with caution when used for individual screening scores, as it has been recommended for research rather than as a diagnostic tool in clinical practice (Ziska, 2024).

*KIDSCREEN-10:* 10 items measure global Health-Related Quality of Life for monitoring and screening purposes (Ravens-Sieberer et al., 2010). The questionnaire will be included in self-report (age 8–18) and parent-report versions. KIDSCREEN-10 is a shorter version of the KIDSCREEN-52 which takes about 5 min to complete (kidscreen.org, n.d.). Despite certain criticisms relating to the psychometric properties of the Danish version of the KIDSCREEN-10 (Nielsen et al., 2023), it was selected over other well-being questionnaires such as the Strengths and Difficulties Questionnaire (Goodman, 2001) to obtain self-report measures.

*Activity Perception Questionnaire* consists of 25 items rated on a 6-point Likert scale and is adapted to this context based on the survey by Deci et al. (1994). Selected items will be used to evaluate and monitor teacher adherence and intervention fidelity, motivation and perception of intervention content (Beaven et al., 2017).

### Participant timeline

2.8

The intervention and assessment timeline for children (C), parents (P) and teachers (T) is presented in Figure 1:

**Figure 1 fig1:**

Intervention and assessment timeline.

Baseline assessments take place immediately before the intervention (t_0_) and post assessments immediately after (t_1_) as mentioned above. Follow-up assessments (t_2_) take place 3-4 months after intervention completion.

### Analytic sample and sample size

2.9

Power calculations are based on the effect sizes reported in comparable intervention studies using the d2-R Attention test as the primary outcome. Schmidt et al. (2015) estimated the effect size needed to achieve statistical significance to reject the null hypothesis based on studies by Gallotta et al. (2012, 2015) using the d2 paper and pencil test. Schmidt et al. (2015, p. 435) present an “*a priori* power analysis with power (1 – beta error probability) = 0.80, alpha error probability = 0.05, effect size *f* = 0.10 [*d* = 0.20], number of groups = 2, number of measurements = 3, and correlation between the repeated measures *r* = 0.75.” This power calculation resulted in a sample size of *N* = 82 students. Schmidt et al. (2015) themselves achieved a medium effect size of *f* = 0.404 (*d* = 0.81). Based on these findings, we chose a minimal detectable effect size of *d* = 0.4, aiming to strike a balance between detectability and feasibility (Dong and Maynard, 2013).

Given that each school will contribute 1 year group consisting of two to three class groups into the intervention and control groups, we must consider the effects of nesting and intra-class correlation coefficient (ICC). The ICC can be defined as follows:

$$\mathrm{ICC}=\frac{\sigma_{\text{class}}^{2}}{\sigma_{\text{class}}^{2}+\sigma_{\text{school}}^{2}+\sigma_{\text{residual}}^{2}}$$

The ICC can be interpreted as the share of the total variance accounted for by the variance between clusters and expresses the strength of the similarity of results within clusters compared with the similarity between clusters (Dreyhaupt et al., 2017).

Based on our pilot project data using the d2-R test on 79 children from eight classrooms in three schools, we ran a linear mixed model in R and found ICC_school_ = 0.00 and an ICC_class_ 0.09. Because this ICC is relatively unreliable, as it is based on a small number of clusters, we also refer to Murnane and Willett (2011), who highlighted that a medium sized ICC is *ρ* = 0.09. The advantage of having based the power calculations on our pilot data is that these children are similar in age and come from a mixed socio-economic background.

According to national statistics, there are 21 children per class on average (Ministry of Children and Education, 2024a), and based on the pilot test we assume that we will get parental consent to take part in tests from around 75% of a class group. We expect an additional attrition across t_1_ and t_2_ of 10% and exclude participants in accordance with the d2-R manual (Hogrefe, n.d.). Thus, we calculate the statistical power based on an effective class group size of 14 individuals.

To find the sample size required to detect a minimum effect size of *d* = 0.4, we used PowerUp (Dong and Maynard, 2013). In addition to the ICC values mentioned above, we calculated the minimum number of schools (level 3 units) to be recruited, by including the proportion of group-level variance explained by covariates such as baseline performance, age and gender (level 1) and school size, grade point average and absence (level 3) (Ministry of Children and Education, 2024b). Including these covariates reduces the group-level residual variance and thereby increases the statistical power (Murnane and Willett, 2011).

As shown in Table 4, we need a total of 12 schools to achieve sufficient power to detect an effect of size *d* = 0.4. To account for attrition at the school level, we plan to recruit a total of 16 schools that will be randomly assigned to intervention and wait-list control groups.

**Table 4 tab4:** PowerUp calculation of sample size including assumptions and comments.

Factors and Assumptions	Values	Comments
MRES = MDES	0.40	Minimum Relevant Effect Size = Minimum Detectable Effect Size
Alpha level (α)	0.05	Probability of Type I error
Two-tailed or One-tailed test?	2	
Power (1-β)	0.80	Statistical power (1–probability of Type II error)
Rho_3_ (ICC_3_)	0.00	Proportion of variance in outcome between Level 3 units: V3/(V1 + V2 + V3)
Rho_2_ (ICC_2_)	0.09	Proportion of variance between Level 2 units: V2/(V1 + V2 + V3)
*P*	0.50	Proportion of Level-3 units randomized to treatment
*R* _1_ ^2^	0.60	Proportion of variance in Level 1 outcome explained by the Level 1 covariates
*R* _2_ ^2^	0.20	Proportion of variance in Level 2 outcome explained by the Level 2 covariates
*R* _3_ ^2^	0.10	Proportion of variance in Level 3 outcome explained by the Level 3 covariates
g_3_*	1	Number of Level 3 covariates
n (Average sample size for Level 1)	14	Mean number of Level 1 units per Level 2 unit (harmonic mean recommended)
J (Average sample size for Level 2)	2	Mean number of Level 2 units per Level 3 unit (harmonic mean recommended)
M (Multiplier)	3.15	Automatically computed
K (Sample Size [# of Level 3 units])	**12**	Number of Level 3 clusters needed for given MDES.

Light yellow values are commonly adopted levels and are preset (Dong and Maynard, 2013). The parametres in dark yellow are specified to the On Track 2.0 study.

### Recruitment and randomization

2.10

Schools will be invited to participate through a combination of e-mails, newsletters and social media to teachers and school principals across the country. Representativeness of the participants is crucial to the external validity of the intervention (Glasgow et al., 1999). We plan to recruit schools from diverse municipalities, which will be randomized into intervention and teaching-as-usual waiting list control groups using a computer-generated random sequence unavailable to those enrolling and assigning schools. All recruited schools will be randomly allocated to avoid skewing results by including a highly motivated experimental group (Conrad, 1987). Ideally, to minimize bias, both program providers (teachers) and pupils should be blinded to whether they are in a treatment or control group (Schulz and Grimes, 2002). While complete blinding is challenging to achieve in psychological intervention studies, every effort well be made to maintain objectivity in the process. When including a waitlist control group, blinding teachers is not feasible to achieve. However, data collection and analyses will be conducted by different people, and analyses will be conducted on anonymized data by a researcher, who is blinded to group membership.

### Data management and analysis

2.11

All data collected during this project will be stored on secure servers provided by the University of Copenhagen. Data handling will strictly adhere to GDPR regulations. A data management risk assessment has been completed. Data management agreements with companies used for data collection (Forstå, Hogrefe, and SurveyXact) have been made.

Data analysis will commence once all data has been collected.

### Ethical considerations

2.12

The Ethics Committee at the Department of Psychology, University of Copenhagen, approved the project (Approval No. IP-EC-25102024-1). When a class is enrolled in the study, parents receive information about the project and the assessments. Only children with written parental consent are included in assessments.

### Data analysis

2.13

Statistical analyses will be conducted to examine the effects of the On Track 2.0 intervention. Descriptive analyses will be conducted of pupil, classroom, and school characteristics and of teacher adherence to the intervention.

The primary outcome, the d2-R concentration scores, will be analyzed in a three-level hierarchical linear model (West et al., 2022), with Age, Sex, and Performance at baseline included as covariates. The secondary outcome, well-being, will be analyzed in a similar fashion. Research question RQ1a will be tested with a comparison of the primary outcome variable between intervention group and control group measured at post-intervention. Research question RQ1b will be addressed with the same group comparison but based on the measurement of the primary outcome at follow-up. Research questions RQ2a and RQ2b involve the same group comparisons at post-intervention and follow-up, tested on the secondary outcome variable (child-reported well-being). We plan to test for the effect of the second level (classes within schools) and remove it from the model, if nested model comparisons do not significantly improve the model fit of the three-level model.

Exploratory analyses connected to RQ3 and RQ4 will include well-being questionnaires completed by parents and teachers, subdomains of d2-R and stop signal task performance, the intervention dosage if possible (e.g., number of lessons completed), and additional covariates.

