The goal of improving EF and well-being through On Track 2.0 is explored through the following four research questions (RQs):

RQ1a: Can the On Track 2.0 intervention improve EF in Danish 4th and 5th grade pupils from pre-to post-intervention assessment?

RQ1b: Is the potential EF improvement of the On Track 2.0 intervention sustained until or increased at the follow-up assessment?

RQ2a: Can the On Track 2.0 intervention improve child-reported well-being in Danish 4th and 5th grade pupils from pre-to post-intervention assessment?

RQ2b: Is a potential improvement in well-being sustained at the follow-up assessment?

In addition, we will explore the following research questions:

RQ3: Do mechanisms such as age, gender, dosage or baseline performance affect either outcome?

RQ4: Does the intervention affect other variables measured such as subdomains of the psychometric tasks (d2-R and Stop Signal Task) or parent-and teacher-reported EF and well-being?

The following sections detail the intervention design, content, and assessment methods and strategies employed to ensure adherence and minimize bias.

On Track 2.0 is a 10-week cluster-randomized, teacher-led intervention integrated into regular classroom teaching. The target group is 4th and 5th grade pupils at standard Danish primary schools. Following the recommendations by Campbell et al. (2000) for complex health interventions, the study consists of four distinct phases. Based on a solid theoretical foundation, Phase I involves designing, modeling and qualitatively testing the content and details of the intervention. During this phase, editors at publishing company Forstå, who provide freely available online teaching materials to schools, assist practically with designing and setting up the intervention content on the online platform while offering didactical feedback.

Phase II entails an exploratory trial, which will include a design and feasibility testing involving a small number of classrooms. Different variations of the content may be tested and focus group interviews with teachers and pupils will inform the adaptation of the material prior to the RCT.

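### The follow-up comparison named for RQ1b answers only part of it: it cannot show an increased effect or tell full retention from partial decay

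*Protocol article*

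**What the plan says.** The Introduction of the protocol article words RQ1b as: "Is the potential EF improvement of the On Track 2.0 intervention sustained until or increased at the follow-up assessment". RQ2b asks the corresponding question for child-reported well-being, but only whether an improvement is sustained; it does not mention an increase.

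Section 2.13 (Data analysis) then assigns a test to each question. For RQ1a: "Research question RQ1a will be tested with a comparison of the primary outcome variable between intervention group and control group measured at post-intervention". For RQ1b: "Research question RQ1b will be addressed with the same group comparison but based on the measurement of the primary outcome at follow-up". For well-being: "Research questions RQ2a and RQ2b involve the same group comparisons at post-intervention and follow-up". The model is a three-level hierarchical linear model "with Age, Sex, and Performance at baseline included as covariates".

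No arm-by-time term, t2-minus-t1 contrast or retention criterion is given. The exploratory analyses in the same section are tied to RQ3 and RQ4 and list no such contrast. Table 4 sizes the trial for a single between-group comparison at d = 0.40.

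**The concern.** Both limbs of RQ1b are relative to t1: an effect can be sustained or increased only in comparison with what it was at post-intervention. The named analysis adjusts for baseline but does not involve the t1 effect. A t2 difference of a given size gives the same result whether the effect has halved, held or doubled since t1.

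Persistence is one of the trial's main questions, and a third on-site assessment is planned to study it. As written, that assessment can establish that a benefit over control is present at t2. It cannot establish how that benefit compares with the one at t1. This is not a detail left to an analysis plan, because the article names the test for RQ1b, and an analysis plan that followed it would carry the mismatch forward.

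**Working it through.** **Inputs from section 2.9 and Table 4.** School ICC 0.00; class ICC 0.09; R² at level 1 = 0.60 and at level 2 = 0.20; 14 pupils per class; 2 classes per school; allocation 0.50; one level-3 covariate; two-sided 5%; 80% power; effect 0.40; K = 12 schools needed, 16 to be recruited. The level-3 R² drops out because the school ICC is zero.

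**Assumed, not in the documents.** The standard error is the same at t1 and t2, and the two effect estimates correlate at r = 0.5 to 0.7.

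**Step 1: reproduce the plan's own figure.**

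SE² = [0.09 × 0.80/(2K) + 0.91 × 0.40/(2K × 14)] / 0.25

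- K = 12: (0.072/24 + 0.364/336)/0.25 = (0.00300 + 0.00108)/0.25 = 0.01633, so SE = 0.128.
- Degrees of freedom = 12 − 1 − 2 = 9. Multiplier = 2.262 + 0.883 = 3.15, as in Table 4.
- Minimum detectable effect = 3.146 × 0.1278 = 0.402. Table 4's 12 schools for 0.40 is reproduced.
- K = 16: SE² = (0.072/32 + 0.364/448)/0.25 = 0.01225, so SE = 0.111, with 13 degrees of freedom.

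**Step 2: what the t2 test responds to.** Its power depends only on the true t2 effect (noncentral t):

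| True t2 effect | 12 schools | 16 schools |
|---|---|---|
| 0.40 | 79.5% | 91.6% |
| 0.20 | 28.8% | 38.8% |

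The 0.40 row is the same whether the t1 effect was 0.80 (halved), 0.40 (held) or 0.20 (doubled).

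**Step 3: whether the t1 and t2 significance results together would serve.** Bivariate normal simulation with the t critical values:

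| True effects (t1, t2) | Pattern | 12 schools | 16 schools |
|---|---|---|---|
| 0.40, 0.40 | t1 significant, t2 not | 11.0% (r = 0.5), 8.6% (r = 0.7) | 5.2% (r = 0.5), 4.1% (r = 0.7) |
| 0.80, 0.40 | both significant | about 81% | about 93% |

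The first row would look like decay when there was none. The second would look like retention when the effect had halved.

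**Step 4: precision of a direct contrast.** SE(change) = SE × √(2(1 − r)); half-width = t(0.975) × SE(change).

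- 12 schools, r = 0.5: 2.262 × 0.128 = 0.29. With r = 0.7: 2.262 × 0.099 = 0.22.
- 16 schools, r = 0.5: 2.160 × 0.111 = 0.24. With r = 0.7: 2.160 × 0.086 = 0.19.
- Power to detect a change of 0.20 with 12 schools: 29% (r = 0.5) or 44% (r = 0.7).

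**The case against.** The strongest reply is that sustained can fairly mean that a benefit over control still exists at follow-up. A baseline-adjusted comparison of randomised arms at t2 estimates exactly that, with about 80% power at 0.40 even if only 12 schools remain. This stands. A reader might infer that RQ1b goes unanswered altogether; the article does not support that.

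A reader might also infer that the team will call the effect sustained when t2 is significant and lost when it is not. The article states a comparison, not a decision rule, and nowhere says that the two significance results will be set against each other. Step 3 therefore shows why that route would fail, not what the plan does. The two estimates could be reported side by side, but without an interval for their difference the reader could not judge whether the effect had changed.

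RQ2b might be thought to share the defect in full. It does not: it has no increased limb, so on the reading above the planned comparison answers it, and only full versus partial retention stays open.

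Finally, the direct contrast has low power for a halving from 0.40 to 0.20. That is true and limits what the fix can deliver. It is a reason to report the interval openly; it does not make the t2 comparison informative about change.

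**Conclusion.** The point holds in a limited form. For RQ1b, the article names a test that covers one part of the question (is there a group difference at follow-up?) and leaves two parts without any stated analysis: whether the effect increased, and whether it was retained in full or only in part. RQ2b is affected only on the last of these. RQ1a and the sample size are untouched.

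That the t2 result does not depend on the t1 effect follows from the stated design; the 80% and 92% figures rest on Table 4 inputs. The 9–11% and 4–5% figures, and the interval widths, rest also on the assumed correlation and equal standard errors. A smaller correlation would raise all of them, and a larger one would lower them.

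A reader might go further and infer a multiplicity fault across RQ1a to RQ2b. The article does not support this: it gives 0.05 only in the power calculation, it separates primary from secondary outcome, and error control across questions is commonly left to the analysis plan.

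**What to change.** Fit t1 and t2 in one mixed model with the baseline covariate, arm, time and arm-by-time, and random effects for pupil, class and school. Report the arm effect at t1, the arm effect at t2, and the t2-minus-t1 difference with its 95% confidence interval. Base any statement that the effect was sustained or increased on the t2 effect and that contrast together. Do the same for well-being.

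The alternative is to reword RQ1b to ask whether a group difference is present at follow-up, which the planned comparison already answers.

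The first option costs one additional model and a few sentences. It needs no new data, and section 2.11 says analysis starts only after all data are collected, so it can be specified in time. Its drawback is precision: state in advance that the trial was not sized for this contrast, and give the expected half-width (about 0.22–0.29 with 12 schools, 0.19–0.24 with 16, under the assumed correlations), so that a wide interval is not taken as proof that the effect was unchanged.
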